### Sample Size

The predefined primary outcome measure is the BESAA at postintervention assessment (T2) and follow-up assessment (T3). Similar RCTs assessing body dissatisfaction evaluating the same outcome measure reported a range of small to medium standardized effects sizes with Hedges *g* ranging from 0.25 to 0.4 (eg, [89]) with a standardized minimum important clinical difference (MICD) of 0.2 exceeding the minimum detectable difference of the measures. To detect the MICD or larger, our proposed sample size of n=900 per group would provide in excess of 90% power (two-sided α=.05) for between-group differences at either T2 or T3 with or without a Bonferroni correction for multiple time points. This assumes that dropout does not exceed 20% in any one arm, and is valid for any positive correlation between commensurate measures at baseline (T1) with T2 or T1 and T3. The oversampling includes a COVID-19 contingency plan permitting the sample size to drop to 650 per group should external challenges arise, and further downward revisions in sample size with a tradeoff in power under worst-case scenarios.

### Analysis Plan

The intention-to-treat set of participants will form the primary analysis set. An assessment of the impact of missing data on statistical conclusions will be undertaken using sensitivity analyses.

For the first hypothesis, the data will be analyzed on an intention-to-treat basis using a linear mixed model with baseline measures at T1 as a covariate, randomized group as a two-level between-subjects factor, and study phase (T2, T3) as two-level repeated-measures factor. The statistical model will be hierarchically balanced with the three-way interaction between covariate, phase, and randomized group as the generating class. This structure permits an analysis of covariance prior reasoned comparison between randomized arms at T2 and T3, assessing the parallel lines of assumption, homogeneity of variance assumption, and the use of robust estimates, if needed. Changes within the randomized arm between T1 and T2 and between T1 and T3 will be assessed using the paired-samples *t-*test and effect size quantified with 95% CIs. The reliable change index will be used to determine the percentage of participants reliably improving within each arm.

For the second hypothesis, the nested intervention study comprises state evaluation of body satisfaction and mood immediately before and after each daily video. A component impact analysis will consist of a 2 (pre, post) by 6 (Day 3 to Day 8) fully repeated-measures analysis including linear and quadratic trends for time sequence effects, and a main-effects comparison between components on pre and post change scores. It is not inconceivable that relative effects between days are likely to be small. For an assumed standardized effect of Cohen *d*=0.1, a sample size of n=800 would be needed for 80% power. These data have further value in evaluating adherence and would permit a dose-response effect to be included in a planned subset analysis.

For the third hypothesis, the relationship between adherence (count of daily completion in each of Day 3 to Day 8) and outcome (primary and secondary) at each of T2 and T3 will be assessed using linear regression controlling for baseline covariates. The cardinal nature of adherence permits Helmert effect coding (difference effect coding) to be used to estimate cumulative dosage effects. The relationship between daily engagement and outcome (primary and secondary) at T2 and T3 will be assessed using linear regression controlling for baseline covariates. These latter models will code each daily engagement as a dummy variable, and will permit a comparison between engagement in each activity. A full statistical analysis plan will be written and approved by the Trial Management Group prior to study closure.

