**Video Six: The Color of the Future**

*Key messages:*
By challenging appearance pressures in everyday life, we can reach our full potential.The additive impact of resisting and challenging appearance pressures is large, not only for the individual but also for wider society.
*Reinforcer activities:*
Watch a short video of Putri sharing the four key lessons she learned throughout her journey. Identify which lesson is most important to you and why.Commit to sharing an unedited photo on social media doing something you love.

In addition to detailing the intervention and its development, this paper describes the evaluation protocol for assessing the effectiveness of the intervention among young Indonesian women aged 15 to 19 years through a parallel, two-arm (intervention vs waitlist control) web-based randomized controlled trial (RCT). The decision to utilize a waitlist control condition was informed by recommendations from a National Institutes of Health expert panel [62]. Specifically, it is recommended that the rationale for a comparator group should rest on the primary purpose of the trial. Thus, given that the primary interest of this study was the absolute impact of the intervention rather than the relative impact, and that usual care for body dissatisfaction in Indonesia is no care at all, a waitlist control condition was deemed most appropriate for this purpose. Our hypotheses for this research are: (1) participants randomized to the intervention condition will experience reduced body dissatisfaction, internalization of appearance ideals, and skin shade dissatisfaction, as well as improvements in mood, at postintervention and 1-month follow-up, relative to the waitlist control condition; (2) each video in the *Warna-Warni Waktu* series will elicit immediate state-based improvements in body satisfaction and mood; and (3) greater engagement and adherence in the *Warna-Warni Waktu* intervention will result in greater reductions in body dissatisfaction, internalization of appearance ideals, and skin shade dissatisfaction, as well as greater improvements in mood. This analysis will be exploratory in nature, depending on the participants’ engagement and adherence in the intervention during the trial.

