### Data Monitoring and Management

Data from recruited participants will be downloaded directly from Qualtrics; thus, there is no data entry process to consider. Once downloaded, the data will be confirmed correct by checking that the data values are as expected. Participant responses will be matched over time, and any duplication of responses will be examined, and if found, deleted. No personal details will be requested from participants via Qualtrics, and as such, these data files should be anonymous. However, the files will be screened at the soonest available opportunity to assess for any inadvertent disclosure of personal information in the form of qualitative responses. If identified, this information will be immediately deleted. Downloaded data will be stored on secure university-approved secure cloud storage (ie, OneDrive). When initial screening described above has been completed by two authors (KG and SH), the data file will then be shared with all study authors.

Consent data, containing personal information, will be collected by the research agency. It will be securely stored for 5 years, as stipulated by the ethical committee of Universitas Indonesia. The personal details of consenting parents or participants will not be shared beyond the research agency.

Based on extensive input from young Indonesian women throughout the development of the intervention and the authors’ experience of utilizing similar surveys among young women in Indonesia with no harm identified, no serious adverse effects are expected for this trial. As such, a data monitoring committee was not deemed appropriate or necessary. Should a participant contact any member of the research team regarding any concerns as a consequence of taking part in the research, this will be dealt with promptly. Such incidences will be reported at the earliest opportunity to the first author (KG) by the research agency, discussed in an internal audit, and reported with the study findings.

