Assessment of harm	Assessment of change in primary outcome measure in the intervention condition compared to the control condition, between T1 and T2	Relative improvements in intervention condition: continue with main trial	No difference between conditions: continue with main trial	Relative deterioration in intervention condition: consider trial termination

^a^T1: baseline assessment.

^b^T2: postintervention assessment.

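### The supportive reliable-change analysis counts improvers only, within each arm; it should show both directions and the between-arm difference with a CI

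*Protocol article*

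**What the plan says.** Hypothesis 1, at the end of the Introduction, is comparative: effects are expected "at postintervention and 1-month follow-up, relative to the waitlist control condition". The main analysis matches it. The Analysis Plan specifies an intention-to-treat linear mixed model with the baseline score as covariate, "randomized group as a two-level between-subjects factor, and study phase (T2, T3) as two-level repeated-measures factor", leading to a "comparison between randomized arms at T2 and T3".

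Two supportive analyses follow in the same paragraph:
- "Changes within the randomized arm between T1 and T2 and between T1 and T3 will be assessed using the paired-samples" t-test, with effect sizes and 95% CIs.
- "The reliable change index will be used to determine the percentage of participants reliably improving within each arm".

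On harm, Table 2 (Results) sets a pilot criterion, "Assessment of change in primary outcome measure in the intervention condition compared to the control condition, between T1 and T2", whose red category reads "Relative deterioration in intervention condition: consider trial termination". For the main trial, Data Monitoring and Management says that "a data monitoring committee was not deemed appropriate or necessary", and that concerns raised by participants will be handled, audited internally and reported. The Analysis Plan ends by promising a full statistical analysis plan, which is not at hand.

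**The concern.** The sentence on the reliable change index is a positive choice of direction (improving) and level (within arm). A later analysis plan that followed it literally would give two one-sided percentages with no interval for their difference. The percentage in the intervention arm contains the background rate of large changes as well as any effect, and a within-arm t-test contains any shift that both arms share. Neither supportive analysis therefore answers a hypothesis stated relative to control.

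The second gap is the unfavourable tail. The index is the only analysis described that classifies individual change on the primary scale, and it is described for improvement alone. A favourable mean difference does not by itself show whether the share who clearly worsened is smaller, equal or larger than under control. This matters for a sample that includes 15- to 17-year-olds and an intervention meant for wide release.

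**Working it through.** **1. The plan's own figure (Sample Size).** Inputs: difference 0.2 SD, 900 per group, at most 20% dropout (900 × 0.8 = 720), two-sided alpha 0.05 or 0.025 with Bonferroni. Power = Φ(0.2 × √(n/2) − z).
- n = 900: 0.2 × √450 = 4.243. Power is 98.9% (z = 1.960) and 97.7% (z = 2.241).
- n = 720: 0.2 × √360 = 3.795. Power is 96.7% and 94.0%.

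The stated power above 90% is reproduced. Nothing below alters it.

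**2. Background rate of reliable change.** Assumptions, not in the document: normal change scores, reliability r, correlation ρ between baseline and follow-up. In baseline SD units, cut-off c = 1.96 × √(2(1 − r)), SD of change s = √(2(1 − ρ)), and with no effect each tail is 1 − Φ(c/s).
- ρ = r: c/s = 1.96, so 2.5% per tail, or 18 of 720.
- r = 0.7, ρ = 0.6: 1.518/0.894 = 1.70, so 4.5%.
- r = 0.8, ρ = 0.7: 1.240/0.775 = 1.60, so 5.5%.
- r = 0.9, ρ = 0.7: 0.877/0.775 = 1.13, so 12.9%.

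For ρ lying 0.1 to 0.2 below r, with r from 0.7 to 0.9, the range is 4.5% to 12.9%.

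**3. Adding a 0.2 SD effect.** Improved = 1 − Φ((c − 0.2)/s); deteriorated = Φ((−c − 0.2)/s).

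| r, ρ | Control improved / deteriorated | Intervention improved / deteriorated | Differences (points) |
|---|---|---|---|
| 0.8, 0.8 | 2.5% / 2.5% | 5.0% / 1.1% | +2.5 / −1.4 |
| 0.8, 0.7 | 5.5% / 5.5% | 9.0% / 3.2% | +3.5 / −2.3 |
| 0.9, 0.7 | 12.9% / 12.9% | 19.1% / 8.2% | +6.2 / −4.7 |

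The intervention percentage alone exceeds the attributable gain in every row; the difference is the informative figure. For the middle row with 720 per arm, the 95% half-width is 1.96 × √((0.055 × 0.945 + 0.090 × 0.910)/720) = 2.7 points for improvement and 1.96 × √((0.055 × 0.945 + 0.032 × 0.968)/720) = 2.1 points for deterioration. An interval is needed to read either difference.

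**4. What the unfavourable tail adds.** A pure mean shift, as in step 3, lowers deterioration, so that table does not illustrate hidden harm. The tails part company if responses vary more under intervention. At r = 0.8, ρ = 0.7, the 0.2 SD benefit leaves deterioration equal to control once the SD of change is (1.240 + 0.2)/1.240 = 1.16 times the control value. Beyond that, more participants deteriorate than under control despite a better mean. An improvers-only report cannot show this.

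**5. Within-arm t-tests.** Assume no intervention effect and a common drift d. Standardised change = d/√(2(1 − ρ)), n = 720, noncentral t.
- d = 0.05 SD: significant with probability 0.27 (ρ = 0.5) to 0.56 (ρ = 0.8).
- d = 0.10 SD: 0.76 (ρ = 0.5) to 0.99 (ρ = 0.8).

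The same drift appears in the control arm and cancels in the mixed model.

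**The case against.** The case against is substantial, and most of it stands.

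- A reader might infer that the randomised comparison is thrown away. It is not: the analysis of hypothesis 1 is a between-arm intention-to-treat model and the sample size is set for it. Nothing makes the t-tests or the index a basis for the conclusion.
- A reader might infer that natural fluctuation will pass as benefit. The percentage is to be given in each arm, so the waitlist figure shows the background rate. What is missing is the stated difference and its interval. The index also screens out measurement error, though not true fluctuation or shared drift.
- Regression to the mean gives no reason to expect a shift in arm means. The Eligibility Criteria set no threshold on body dissatisfaction.
- A reader might infer that the main trial abandons the pilot's harm signal. That signal is a group-level contrast on the BESAA, and the two-sided comparison of arms at T2 and T3 in effect repeats it. The baseline-by-phase-by-group interaction also examines effects that differ by baseline level, and participants' concerns will be reported.
- Saying that deterioration will never be counted goes too far. The article states no such count; the full analysis plan may define one.

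The deferral to a later plan does not dispose of the point. Cut-off and reliability source can properly wait, but the article has already fixed direction and level.

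**Conclusion.** The point holds as a low-cost improvement to a supportive analysis and to harm reporting. It is not a flaw in the primary inference, and stated power, alpha and sample size are unaffected. As described, the individual-level analysis is one-sided and within arm, with no between-arm contrast and no deterioration percentage, and the paired t-tests beside it are not evidence of an intervention effect.

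The size can only be given as a range, because reliability and correlation are assumed: with no effect, 2.5% per tail if they are equal and roughly 4.5% to 13% if the correlation is 0.1 to 0.2 lower. A claim that the within-arm percentage overstates benefit by a fixed factor is not supported. The factor depends on the assumed pair, and arises only if the control percentage is ignored.

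**What to change.** In the statistical analysis plan, for T2 and T3:
- Classify each participant as reliably improved, unchanged or reliably deteriorated on the BESAA, and report all three percentages in both arms.
- Give the between-arm risk difference with 95% CI for improvement and for deterioration. Name the deterioration contrast as a harm summary for the report; no stopping rule is implied.
- Label the within-arm changes and paired t-tests as descriptive, with conclusions on hypothesis 1 drawn from the mixed model.

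The cost is a few lines of analysis and one table on data already being collected. Alpha, sample size and the primary analysis do not change.

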On the morning of the third day (Day 3), participants in the intervention condition will be sent their PIN and a link to the first video (and associated activity). Again, participants will be requested to enter their PIN on the first page of the link. Participants will complete state measures of body satisfaction and mood before watching the first video in the *Warna-Warni Waktu* series. State measures of body satisfaction and mood will be asked again immediately after the first video. Next, participants will be presented with the activity for the first video. Before exiting the link, participants will be asked to report on the strength of their internet connectivity while watching the video (see the Measures section below). This process is repeated on Days 4-8 for the remaining five videos (and associated activities). Participants will not be sent reminders to view or engage with the content in these links.

On Day 9 of the study (again, in the morning), participants in both conditions will be sent a link to complete the second assessment. As with the baseline assessment, participants will be given 24 hours to complete this assessment, with reminder messages sent to noncompleters after the first 8 hours. The same process will be executed for the third and final assessment, 1 month later on Day 36. Following the third assessment, all participants will be debriefed on the study aims and provided with additional sources of mental health support, as well as a certificate of participation. Participants who complete all three assessments will be rewarded with Rp125,000 (approximately US $8.75) to encourage participant retention. By this point, the responses to the four 250-word writing activities will have been judged, and those who have won will be contacted and will receive their prize. Those in the waitlist control condition will be provided with a link to the *Warna-Warni Waktu* video series on Day 37. Participants in the waitlist control condition will not be assessed for their engagement with the content. Information sheets and the participant debrief document can be found in Multimedia Appendix 4.

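### The Helmert coefficients planned for hypothesis three are neither cumulative nor per-video effects, and self-selected completion supports an association only

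*Protocol article*

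**What the plan says.** The third hypothesis, at the end of the Introduction, holds that more engagement and adherence in the "intervention will result in greater reductions in body dissatisfaction, internalization of appearance ideals, and skin shade dissatisfaction", together with more improvement in mood. The sentence after it reads: "This analysis will be exploratory in nature, depending on the participants’ engagement and adherence in the intervention during the trial."

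The Analysis Plan (Methods) defines the exposure as "adherence (count of daily completion in each of Day 3 to Day 8" (closing bracket omitted here), which is a count from 0 to 6. Its relationship with the primary and secondary outcomes at T2 and at T3 "will be assessed using linear regression controlling for baseline covariates". The coding and its purpose follow: "The cardinal nature of adherence permits Helmert effect coding (difference effect coding) to be used to estimate cumulative dosage effects." A second set of regressions enters engagement on each day as a dummy variable. A full statistical analysis plan is promised before study closure.

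Under Participant Recruitment and Procedure, the daily links go to the intervention arm only, and "Participants will not be sent reminders to view or engage with the content in these links." The waitlist arm receives its link on Day 37, the day after the last assessment, and "Participants in the waitlist control condition will not be assessed for their engagement with the content."

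**The concern.** The Analysis Plan names a coding, gives a reason for it and says what it will estimate, and these do not fit together. Helmert-type contrasts compare a level with an average of other levels. A cumulative dosage effect compares a level with zero, and a per-video effect compares it with the level just below. A reader who takes the printed coefficients as either would misjudge the shape of the dose-response.

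The second difficulty would remain under any coding. Participants decide for themselves, unprompted, how many videos to complete. Those who complete more may differ in motivation or in readiness to change, and baseline covariates need not capture that. The regression would then credit the videos with differences between kinds of participant, while the hypothesis and the reference to dosage effects are both worded causally.

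**Working it through.** **Inputs.** The count has seven levels, 0 to 6, hence six contrasts (Analysis Plan). The planned arm size is 900, with dropout of up to 20% (Sample Size): 900 × 0.8 = 720. The protocol gives no effect size or power for hypothesis three, so there is no stated figure to reproduce. The neighbouring claim that "our proposed sample size of n=900 per group would provide in excess of 90% power (two-sided α=.05" (closing bracket omitted) does reproduce for a 0.2 SD difference: 98.9% at 900 per arm and 96.7% at 720, or 97.7% and 94.0% at α = 0.025. It concerns the randomised comparison only.

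**Step 1: constant gain.** Assume each video adds δ, so the mean at level k is kδ.

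- Difference (reverse Helmert) coding: level k minus the mean of levels 0 to k−1 = kδ − (k−1)δ/2 = (k+1)δ/2, for k = 1 to 6.
- Forward Helmert coding: mean of levels k+1 to 6 minus level k = (k+7)δ/2 − kδ = (7−k)δ/2, for k = 0 to 5.

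| In units of δ | 1st | 2nd | 3rd | 4th | 5th | 6th |
|---|---|---|---|---|---|---|
| Cumulative effect versus none | 1 | 2 | 3 | 4 | 5 | 6 |
| Step for one more video | 1 | 1 | 1 | 1 | 1 | 1 |
| Difference coding | 1 | 1.5 | 2 | 2.5 | 3 | 3.5 |
| Forward Helmert coding | 3.5 | 3 | 2.5 | 2 | 1.5 | 1 |

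After the first coefficient, difference coding matches neither target. Read as steps, a constant benefit looks like a growing one, or like a shrinking one under forward Helmert.

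**Step 2: other assumed shapes, difference coding.**

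- 0.1 SD per video up to the third, then nothing: 0.10, 0.15, 0.20, 0.15, 0.12, 0.10. The last three videos add nothing, yet their coefficients are not zero.
- 0.3 SD from the first video only: 0.30, 0.15, 0.10, 0.075, 0.06, 0.05, although every step after the first is zero.

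**Step 3: recovery.** All full-rank codings of seven levels are the same six-degree-of-freedom model with the same fit. With difference coefficients b1 to b6, six videos versus none = b1/2 + b2/3 + b3/4 + b4/5 + b5/6 + b6. In the constant-gain case this is (0.5 × 5 + 3.5)δ = 6δ, which is correct. The information is in the model but not in the individual coefficients.

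**Step 4: the stated reason.** A cardinal count has equal, meaningful spacing, which is what a linear term uses. Helmert-type contrasts treat the count as ordered categories and ignore the spacing.

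**Step 5: self-selection.** A simulation used n = 720, 400 runs and a true video effect of zero. Its assumptions were a standard normal engagement trait U that is not measured; completion binomial out of 6 with log-odds 1.5 + U; and outcome = 0.6 × baseline + g × U + noise, with total variance 1. Outcome was regressed on baseline and the count.

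| g (SD of outcome per SD of U) | Mean slope per video (SD) | Rejected at 5% |
|---|---|---|
| 0 | 0.00 | 5% |
| 0.1 | 0.05 | 63% |
| 0.2 | 0.10 | 99% |
| 0.3 | 0.15 | 100% |

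A modest unmeasured trait is enough to produce a convincing slope from nothing. The protocol gives no value for g, so the rows show a range and not a forecast.

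**The case against.** The strongest reply on the coding is that cumulative effects can be computed exactly from the planned model (Step 3), so it would be wrong to say that the model cannot estimate them. That stands. The point is confined to what the coefficients mean as printed, and the plan describes no recombination.

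Terminology is a second defence. Conventions for Helmert coding differ, and the bracketed gloss may be meant to say which version applies. If adjacent differences were intended, the coefficients would be per-video steps that sum to the cumulative effect, and this part of the point would reduce to unclear wording. The text does not settle which is meant.

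On causality, the hypothesis is expressly exploratory, the Analysis Plan speaks of a relationship, and a hypothesis is not a planned conclusion. This lowers the weight of the point. It does not dispose of it: the exploratory label limits how strongly a result is claimed but neither removes self-selection nor corrects a mismatched contrast, and the Analysis Plan itself refers to dosage effects. The promised analysis plan is a good place for the repair, but the method criticised is one the protocol already states.

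Four stronger readings are tempting and not supported:

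- A reader might infer from Table 2 that at least 80% are expected to complete all six videos, leaving the lower levels nearly empty. The 80 is the green progression threshold for the 150-person pilot, not a forecast for the main trial.
- A reader might infer that the coding creates a dose-response where none exists. If the mean outcome is the same at every level, every contrast is zero. The coding distorts the shape of a real gradient, and a spurious gradient comes from self-selection.
- A reader might set the precision of adjacent-level contrasts against the 0.2 difference under Sample Size. That figure was set for differences between arms and is no benchmark for one video.
- A reader might infer that the result would decide how many videos are disseminated. The protocol ties dissemination to whether the intervention is effective and nowhere links the number of videos to this analysis.

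**Conclusion.** The point holds in limited form. Under the Helmert or reverse-Helmert reading, the coefficients are not the cumulative dosage effects the plan says they will estimate, nor per-video effects. With a constant gain they span a 3.5-fold range where the true steps are equal. That size is exact arithmetic given the assumed shape. It falls away if successive differences were meant.

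Separately, and under any coding, a regression on self-selected completion adjusted only for baseline covariates gives an association. It cannot carry the causal wording of hypothesis three. How large the bias would be is unknown; the simulated 0.05 to 0.15 SD per video rests on assumed trait strengths of 0.1 to 0.3 SD and an assumed completion model. The analysis is read here as within the intervention arm, because completion is recorded only there.

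The correction is worth making before the analysis plan is approved. The randomised comparisons at T2 and T3 are unaffected.

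**What to change.** - **Coding.** Use one linear term for the count, plus successive-difference contrasts (for steps) or level-versus-zero contrasts (for cumulative effects). Define them by formula and not by name alone. Collapse levels that prove sparse, by a rule fixed before unblinding.
- **Wording.** Restate hypothesis three so that greater adherence will *be associated with* greater improvement, and replace the reference to dosage effects. Report the daily-engagement dummy models in the same terms, since they share the self-selection.
- **Supplementary causal estimate.** Estimate the average per-video effect, or the effect in compliers, by two-stage least squares with randomised arm as the instrument and baseline score as covariate. The waitlist dose is zero through T3, because that arm's link comes on Day 37. State the linearity assumption and the exclusion assumption (assignment acts on outcome only through the videos and activities completed). The latter needs comment because participants are unblinded and outcomes are self-reported. This gives one average effect, not a dose-response shape.

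The cost is a few lines in the analysis plan and one extra model on data already planned for collection. The instrumental-variable estimate will be less precise than the simple regression, and the report should say so.
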